Thus far this research has been relatively limited to ‘Western’ contexts. This study aims to extend this research on grammatical gender and to test whether masculine generics in other language families, specifically Arabic, behave similarly to Indo-European languages. Arabic is one of the most spoken languages around the world, and yet research on the processing of Arabic grammatical gender remains relatively understudied. Additionally, the use of masculine generics in Arabic speaking countries, especially in the context of job recruitment and formal settings, is largely unquestioned and widely accepted as equally representative of all genders. However, a recent study on the language used in Egyptian job recruitment and advertising showed an overuse and inconsistent use of masculine generics, where stereotypically male-dominated industries used masculine generics and stereotypically female-dominated jobs were advertised in feminine grammatical gender regardless of the gender targeted for the role [11]. Additionally, the study showed that jobs were advertised in both singular (majority) and plural masculine generics, and so a key aspect of this investigation is to determine whether masculine generics in singular or plural are interpreted more or less strongly as male-referring. Therefore, the overall aim of this study is to explore how the presence or absence of grammatical gender affects gender representation in perception.

Specifically, the primary objective of this study is to investigate the role that morphological gender marking plays in either entrenching or perhaps mitigating these segregated and polarised recruitment patterns. To do so, we explore the following questions:

1. How does grammatical gender mediate referent expectations in the presence of competing social information?
a. Do singular masculine generics create a male bias in perception, and are these biases different in singular and plural masculine generics?b. Do participants rely more on stereotypical social information or grammatical information to inform their occupational expectations?c. If the social and grammatical cues conflict, do participants exhibit processing costs? Or is there a processing benefit to having congruent social and grammatical cues? And are these benefits or costs consistent across different gender and cue-type combinations?

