Similarly, in condition 4 (neutral English), stereotypical information may inform participants’ gender expectations, such that *doctors* are more likely to be men and *secretaries* are more likely to be women in responses. If this is the case, then the fixed effect for language in conditions 3 and 4 should not be statistically different. Importantly, in this condition participants have the option to respond in the gender neutral ‘they’ instead of assuming the role’s gender. Therefore, some variation between feminine, masculine, and neutral pronouns could be expected. If this condition also elicits highly gendered responses based on social stereotypes, then this presents evidence on the importance of gender-fair and representative language rather than just neutral language. This has implications for jobs advertised in English, which are assumed to be gender-neutral in interpretation but may instead entrench participant’s existing stereotypes.

Additionally, it is expected that fluency measures in congruent conditions will exhibit processing benefits (i.e., fewer fluency mistakes, more speech produced within the time limit, less hesitation, and reduced lag time) compared to their incongruent counterparts. Where grammatical information and stereotype information are incongruent (i.e., *nurse* presented in the masculine or *manager* presented in the feminine), it is predicted that outcomes related to fluency and initial response time will be negatively affected and participants will experience processing costs as a result of a violation of expectations. Importantly, interpreting masculine G-gender as generic should not be as costly or inefficient because it can be used to refer to male or female S-genders.

Further, condition 3 should not show significant differences in fluency or response time due to stereotype or number variation. This is because G-gender and stereotype information can always be congruent in a word-pair. Similarly in condition 4, it is predicted that fluency and response time will not vary across stereotype or number.

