## Pre-specified analysis plan

The study uses mixed effects regression, modelled in STATA, to account for within and between variation in the experiment. There are two different outcome categories and therefore multiple models will be used to explore the effect of language on the dependent variables outlined above.

The first set of models related to fluency will utilise linear-mixed-effects models, and models related to gender expectations will use generalised linear mixed effects models for categorical dependent variables. In both cases, the language condition will be defined as the fixed effect. The models will include random slopes for this fixed effect as some occupations may be more affected by the language condition than others. By-participant random slopes and intercepts will be included in the models as random effects. This is because participant variation is expected due to differences in demographic information (age and gender), attitudes towards women (from the exit survey), language dominance measures (exit survey), and participant’s nationality (note that this is likely corelated with attitudes towards women, and highly correlated with language dominance measures). Similarly, by-item random slopes and intercepts will be included as variation due to length of stimuli or familiarity with different occupations should be accounted for.

Interaction effects will be explored between stereotype and language condition, and for a subsample of the data interactions between number and stereotype will also be explored. Interaction effects related to number will help assess the mediating effect of number on gender expectations in masculine grammatical gender.

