### Data processing & cleaning

In this section we describe how we handle outliers, missing data, and model specification. Firstly, given the presence of by-item and by-participant slopes and intercepts, outliers are less likely to be problematic for the analysis. However, as an additional check, using the *extremes* command on STATA for all numeric outcomes (i.e., fluency measures) we will initially check for cases with extremely high or low values. If any extreme values are identified, they will be investigated further by checking their residuals and leverage. A sensitivity analysis will be conducted to determine whether outlier data will be included or excluded in the analysis. If results are heavily affected by the inclusion of an outlier (and there is no evidence to suggest that differences in results are not random) then this data will be excluded from the analysis.

Secondly, if there is more than 5% of the data missing, this will be further investigated to check if by-item attrition is systematic or randomly distributed. If it is randomly distributed, then these missing observations are automatically removed by STATA in analysis. However, if the missing observations are systematic (e.g., most of the missing data is in response to one particular occupation or stimuli) then this will be investigated further and potentially dropped from the analysis.

Finally, to avoid an overspecification of the models, models that include interactions as predictors will be compared to a simplified model that excludes these interactions using the Bayesian Information Criterion (BIC). The BIC will be used to determine if the unrestricted or restricted model is a better fit for the data.

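### BIC may remove the language x stereotype interaction, the term that carries the fluency congruence predictions, and it sets a far stricter bar than the protocol's own alpha

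*Protocol article*

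**What the plan says.** Under Data processing & cleaning, to guard against overspecified models, "models that include interactions as predictors will be compared to a simplified model that excludes these interactions using the Bayesian Information Criterion (BIC"), and "The BIC will be used to determine if the unrestricted or restricted model is a better fit for the data". The rule covers interactions generally and exempts none.

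The Pre-specified analysis plan describes the fixed part briefly: "In both cases, the language condition will be defined as the fixed effect". Stereotype is mentioned there only through the interaction: "Interaction effects will be explored between stereotype and language condition".

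Elsewhere the same interaction has a larger role. Question 1c, under the primary objective in the Introduction, asks: "If the social and grammatical cues conflict, do participants exhibit processing costs"? It goes on to ask whether congruent cues help and whether any effect is the same across combinations. The Hypotheses section answers in advance that "fluency measures in congruent conditions will exhibit processing benefits", with costs in the incongruent cells, and that "condition 3 should not show significant differences in fluency or response time due to stereotype or number variation". Table 5 sets out the direction for each fluency outcome. Outcomes of interest adds that a female-associated role in masculine form should carry no cost if the masculine really is generic.

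**The concern.** For the fluency outcomes, congruence is not a property of the language condition or of the stereotype alone. It is defined by their combination, so in a model with these two factors it is the language x stereotype interaction. A rule written to trim surplus terms is therefore also the rule that decides whether a prediction under the primary objective remains in the model.

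Two things are at stake. First, if BIC prefers the simpler model, the reported model has no term for the predicted crossover. Second, the error has a direction. A model without the interaction could be read as showing no stereotype cost for masculine forms, or as confirming the predicted absence of stereotype differences in the word-pair and English conditions, when the term was simply not retained.

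**Working it through.** **1. Plan's own figure and inputs.** Sample size: 4 x 30 + 30 + 30 = 180, as stated. The singular Arabic component (blocks 1–3) has 3 x 30 = 90 participants with 12 role nouns each, so 90 x 12 = 1,080 trials. Table 2 spreads these evenly over 9 language-by-stereotype cells: 1,080 / 9 = 120 per cell. The Sample size section names power 0.9 and alpha 0.1 for the post-pilot power analysis and says that no effect size can be estimated yet.

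**2. What a model without the interaction can show.** Code the Table 5 prediction for words produced as high = +d/2 and low = −d/2, with word-pairs at 0 because no stereotype difference is predicted there.

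| | male role | female role | neutral role | mean |
|---|---|---|---|---|
| masculine | +d/2 | −d/2 | +d/2 | d/6 |
| feminine | −d/2 | +d/2 | +d/2 | d/6 |
| word-pair | 0 | 0 | 0 | 0 |

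The masculine and feminine means are equal, so the crossover contributes nothing to the difference between them. Without an interaction, the male-minus-female contrast is forced to be the same in every condition, namely the average (d − d + 0) / 3 = 0. The model would report zero cost within the masculine even though the cost under this pattern is d. If the costs are unequal, c_m in the masculine and c_f in the feminine, the common contrast is (c_m − c_f) / 3, which recovers neither. Adding a stereotype main effect does not help.

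**3. How strict BIC is.** BIC keeps k extra parameters only if the likelihood-ratio statistic exceeds k ln(n). The 3 x 3 interaction has (3 − 1)(3 − 1) = 4 df. The article does not say whether n counts trials or participants, so both are shown.

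- n = 1,080: 4 x ln(1,080) = 27.94; chi-square (4 df) tail 0.000013.
- n = 90: 4 x ln(90) = 18.00; tail 0.0012.

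**4. Probability of keeping an interaction that a direct test would find with 90% power at alpha 0.1.** The required noncentrality for 4 df is 12.88. The probability that a noncentral chi-square with that value exceeds the BIC threshold is:

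| Coding | Noncentrality | n = trials | n = participants |
|---|---|---|---|
| 4 df (3 x 3, blocks 1–3) | 12.88 | 0.09 | 0.40 |
| 1 df congruence contrast | 8.56 | 0.61 | 0.79 |

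The 1-df thresholds are ln(1,080) = 6.98 (p < 0.008) and ln(90) = 4.50 (p < 0.034). For BIC to keep the 4-df term 90% of the time, the noncentrality must be 39.8 or 27.1, that is 39.8 / 12.88 = 3.1 or 27.1 / 12.88 = 2.1 times the information. A sample sized at alpha 0.1 would therefore not match the rule that decides on the term.

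**5. Dependence on effect size.** For the pattern in step 2 the interaction sum of squares is 1.111 d², so the noncentrality is 120 x 1.111 x d², with d in residual SDs. The d values are assumed, since the protocol gives none.

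| d | Direct 4-df test, alpha 0.1 | BIC keeps, n = 1,080 | BIC keeps, n = 90 |
|---|---|---|---|
| 0.2 | 0.55 | 0.005 | 0.07 |
| 0.3 | 0.88 | 0.07 | 0.35 |
| 0.4 | 0.99 | 0.36 | 0.76 |
| 0.5 | 1.00 | 0.78 | 0.97 |
| 0.6 | 1.00 | 0.97 | 1.00 |

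A fixed-effects simulation on the Table 2 layout (1,000 runs per d, n = 1,080) gave similar retention: 0.01, 0.10 and 0.83 at d = 0.2, 0.3 and 0.5. Steps 3 to 5 ignore the planned random slopes.

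**The case against.** The strongest reply has four parts.

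- **BIC is a recognised and conservative guard against overfitting**, there are many outcomes, and the plan says only that these interactions will be explored. This stands for exploratory terms. It does not cover a term for which question 1c, the Hypotheses section and Table 5 state a direction in advance.
- **Frequency of removal.** A reader might infer that the interaction will usually be dropped. The documents do not support that. The 9% and 40% figures apply to an omnibus 4-df term placed exactly at 90% power for alpha 0.1. A single contrast at the same power would be kept more often than not, and under the assumed pattern even the 4-df term is mostly kept from about d = 0.5. Alpha 0.1 is also named only for the power analysis, not for this test. This part stands.
- **Whether it is tested.** A reader might also infer that the congruence predictions would go untested. That is too strong. The comparison requires the interaction model to be fitted and is itself an implicit test, and the protocol does not say that the unrestricted estimates will be withheld. This stands too. The defect is the strictness of the test and the model that is then preferred.
- **Reach.** It is tempting to say that question 1b and every row of Table 5 rest on the interaction. They do not. For gender interpretation in the masculine and feminine conditions, the Hypotheses section predicts that grammatical gender prevails whatever the stereotype, which is a condition effect. Outcomes of interest also derives a stereotype-congruence outcome whose overall level helps answer 1b. The singular-masculine part of 1a and the overall word-pair effect likewise survive in the simpler model.

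**Conclusion.** The point holds for the fluency models. The protocol submits the language x stereotype interaction to BIC without exemption, although that term carries the congruence predictions and the check that masculine forms impose no cost on female-associated roles. Without the term, those contrasts cannot be recovered. The implied significance threshold for the 3 x 3 interaction is 0.000013 or 0.0012, depending on how n is counted, against the 0.1 used for planning.

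The size of the loss is conditional. The retention figures rest on large-sample chi-square approximations without random slopes, on the coding of the interaction, and on an effect size that the protocol says it cannot yet estimate. Condition main effects and most gender-interpretation predictions are not affected.

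**What to change.** In the Pre-specified analysis plan, state that language, stereotype and language x stereotype stay in every fluency model for the singular Arabic conditions, whatever BIC says. Name the congruence contrasts to be reported with estimates and intervals: male versus female roles within the masculine, the same within the feminine, and the difference between the two. Under Data processing & cleaning, limit BIC to exploratory terms such as number x stereotype.

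This takes about two sentences, to be settled before the data are analysed. The statistical cost is four interaction parameters in about 1,080 trials, plus two for stereotype if it is not already in the model.

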## Timeline

Table 6.
